**Discussion:**

This study aims to explore potential associations between GLP-1 RA use and changes in IPMN characteristics, tumour markers, and disease progression. Given the retrospective design and expected small sample size (estimated at 30–60 patients in total), the study may not be powered to establish definitive correlations. Nonetheless, it will generate preliminary data to help inform hypotheses and guide future research. Any observed trends could provide valuable insights into the safety of GLP-1 RAs in patients with IPMNs and contribute to more informed clinical decision-making regarding the use of these agents in a population at risk for pancreatic disease progression.

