**Fig 1 pone.0357577.g001:**
[figure not shown]
Study design and comparison groups. Schematic overview of the retrospective multicentric cohort study evaluating the impact of GLP-1 RA therapy on patients with IPMNs. Four study groups will be included according to IPMN diagnosis and GLP-1 RA exposure: patients with IPMN treated with GLP-1 RAs, patients with IPMN not treated with GLP-1 RAs, patients without IPMN treated with GLP-1 RAs, and patients without IPMN and without GLP-1 RA exposure (general population). The primary outcome (1) is the progression of radiological IPMN characteristics according to the Kyoto 2023 Consensus criteria. Secondary outcomes include longitudinal changes in serum CA19−9 and CEA levels (2) and the incidence of acute pancreatitis (3). We hypothesize that GLP-1 RA therapy is not associated with an increased progression of IPMN radiological features or adverse pancreatic outcomes compared with patients not exposed to GLP-1 RAs.

A list of patients diagnosed with IPMNs will be compiled (List A), and this group will then be cross-referenced with data from patients who have been treated with GLP-1 RAs (List B). ICD-10 codes, keywords like IPMN and ATC medication codes will be used to identify the patients and compile the two lists (S1 File). This method will allow us to identify the subset of patients in whom both IPMN and GLP-1 RA treatment are present. The same number of patients will be randomly extracted from the two lists. For example, if 3 patients with GLP1-RA and IPMN are extracted in the HFR dataset, then 3 patients will be extracted in List A and 3 in List B. The same procedure will be carried out for the other two institutions. For the no GLP-1 RA & no IPMN group, the proportion of AP will be generalized to the incidence in the general population.

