### Sample size and statistical analysis

#### Sampling plan.

The sample size is expected to be between 10 and 20 patients for the condition with GLP-1 RAs and IPMN, due to the rare nature of the patient population with both IPMN and GLP-1 RA use. The other conditions (GLP-1 RA & no-IPMN, no GLP-1 RA & IPMN) will match in sample size the above-mentioned condition as it is the most stringent. This design ensures to isolate the interaction effect of GLP-1 RA and IPMN while ensuring proper statistical power. Indeed, a-priori power analysis computed with G*Power [22] shows that for our smallest estimation of effect size (i.e., 10–30 patients per condition, 30–60 in total), a 2x2 ANOVA detects a significant medium effect size with a power if 80% and an alpha of 0.05.

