#### Analysis plan.

H1) We expect significantly more occurrences of change in at least one of the criteria from the Kyoto 2023 Consensus (see Outcomes section) [1] from patients with GLP-1 RA & IPMN than patients with no GLP-1 RA & IPMN, as assessed by a one-sided test of two proportions. H2) We expect significantly greater changes in the CEA (H2a) and CA19−9 (H2b) serum tumor markers over time induced by GLP-1 RA, as assessed by the interaction term of the within-factor Time and the between-factor Group (GLP-1 RA & IPMN vs. no GLP-1 RA & IPMN). H3) We expect significantly different incidence of AP driven by GLP-1 RA and IPMN, as assessed by a Chi-square test across all conditions (GLP-1 RA & IPMN, no GLP-1 RA & IPMN, GLP-1 RA & no IPMN).

Timing of progression: T0 will be defined as the first available follow-up examination for patients with IPMN who were not treated with GLP-1 RAs, and as the first available follow-up examination after initiation of GLP-1 RA therapy for patients with IPMN who received GLP-1 RAs.

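### Acute pancreatitis (H3) is to be judged by a chi-square test alone in groups of about 10 to 20; if events are rare, exact intervals would be the better main result at little cost

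*Protocol article*

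**What the plan says.** In the protocol article's Analysis plan, H3 concerns the "incidence of AP" in three groups: GLP-1 RA with IPMN, IPMN without GLP-1 RA, and GLP-1 RA without IPMN. A difference is expected, "as assessed by a Chi-square test across all conditions". The article names no estimate, interval or rule for a table without events for this outcome.

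Group sizes are in the Sampling plan: "The sample size is expected to be between 10 and 20 patients for the condition with GLP-1 RAs and IPMN". The other two observed groups are matched to that number. The power sentence in the same section uses a wider range, "10–30 patients per condition, 30–60 in total".

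The group with neither exposure nor IPMN is not sampled. Under Study design, after Fig 1, "the proportion of AP will be generalized to the incidence in the general population".

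Two statements bear on how the result will be read. The Fig 1 legend hypothesizes that "GLP-1 RA therapy is not associated with an increased progression of IPMN radiological features or adverse pancreatic outcomes". The Discussion paragraph of the Abstract says that "the study may not be powered to establish definitive correlations", and then that "Any observed trends could provide valuable insights into the safety of GLP-1 RAs in patients with IPMNs".

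**The concern.** AP is a safety outcome, and the groups are very small. A chi-square test answers only whether the observed proportions differ more than chance would explain. With no AP case it gives no answer. With one case it gives a p-value that is nearly the same whatever the group size and says nothing about the range of risks that the data leave open.

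The reader of a safety study needs that range. Because the Fig 1 legend hypothesizes no association with adverse pancreatic outcomes, a missing or non-significant test could be taken as support for it, although the data would still allow a large AP risk. The general caveat about power does not tell the reader how large.

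**Working it through.** **Inputs.** Group size n = 10 to 20, three equal groups (Sampling plan); n = 30 is added because the power sentence mentions it. The test is a chi-square on a 3 × 2 table with 2 degrees of freedom (Analysis plan). The article gives no AP risk for any group, so a common risk p of 1% to 10% is assumed. There is no planned figure for H3 to reproduce: the 80% power in the Sampling plan refers to an ANOVA.

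**Step 1. Is the test's false-positive rate acceptable?** All 3 × 2 tables were enumerated and the rejection probability at the 5% level was computed for common risks from 0.5% to 50%. The maximum is 5.0% at n = 10 and 5.2% at n = 15, 20 and 30. The size is acceptable.

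**Step 2. How often is there no AP case at all?** P(no case) = (1 − p)^(3n). For example, 0.99^30 = 0.74 and 0.95^60 = 0.046.

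| Assumed AP risk | n = 10 per group | n = 20 per group |
|---|---|---|
| 1% | 74% | 55% |
| 2% | 55% | 30% |
| 5% | 21% | 5% |
| 10% | 4% | 0.2% |

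In these studies every expected AP count is zero and the statistic is undefined.

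**Step 3. How often is there at most one case?** P(at most one) = (1 − p)^(3n) + 3n·p·(1 − p)^(3n−1). At 1% to 5% risk this is 96% to 55% for n = 10, and 88% to 19% for n = 20.

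**Step 4. What does the test say with one case?** For a 1/0/0 split the expected AP count is 1/3 per group. The squared deviations sum to (2/3)² + 2 × (1/3)² = 2/3. At n = 10, X² = (2/3)/(1/3) + (2/3)/(29/3) = 2 + 0.069 = 2.069, and with 2 degrees of freedom p = exp(−2.069/2) = 0.355. At n = 20, X² = 2 + (2/3)/(59/3) = 2.034 and p = 0.362. The p-value hardly changes when the group size doubles.

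**Step 5. What would exact intervals say?** The upper Clopper-Pearson 95% limit for 0/n is 1 − 0.025^(1/n): 30.8% for 0/10, 16.8% for 0/20 and 11.6% for 0/30. For 1/10 the interval is 0.3% to 44.5%; for 1/20 it is 0.1% to 24.9%.

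For the difference between exposed and unexposed IPMN patients, an unconditional exact score test was inverted (0.025 per tail, largest tail probability over the nuisance risk):

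| Cases (exposed / unexposed) | n = 10 | n = 15 | n = 20 |
|---|---|---|---|
| 1 / 0 | about −21 to +46 points | about −16 to +32 | about −13 to +25 |
| 0 / 0 | excess up to about 31 points | – | excess up to about 18 |

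A repeat on a coarser grid agreed to within about one point. Unlike the p-value, these intervals exist without events and narrow as the groups grow.

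**Step 6. Would another test change the decision?** The mid-p version of the Fisher-Freeman-Halton test gives the same verdict as chi-square at every split with 8 or fewer cases for n = 10, 15 and 20. At n = 30 a few splits differ (3/0/0: chi-square 0.045, mid-p 0.052). The ordinary exact test loses power: for assumed risks of 25%, 3% and 3% it falls from 34% to 15% at n = 10 and from 62% to 55% at n = 20. The gain therefore comes from the intervals.

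**The case against.** The strongest reply is that nothing is wrong with the test. Its size is about 5%, and a mid-p version reaches the same verdicts at the planned sizes. What remains would be a matter of reporting, which a condensed article may leave to the full protocol or analysis plan. With no event the authors would simply report 0/n per group. The article already admits low power and calls its results hypothesis-generating. The frequency of empty tables rests on an assumed risk; at 5% or more with 20 per group they are uncommon. The intervals are so wide that they largely restate the admitted imprecision.

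Most of this stands and limits the weight of the point. It does not remove it. The article itself commits H3 to a test, so the choice of main result has been made and is open to comment. The general caveat about power does not say how much AP risk remains possible; an interval does.

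Three stronger readings are tempting and are not supported:

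- **The test is invalid because expected counts fall below five.** Five expected cases per group would need 15 AP cases in total, which will hardly occur if AP is rare, but Step 1 shows that the false-positive rate is still acceptable.
- **Leaving the general-population group out of the test is an error.** That group is not sampled, so keeping it out of a test on observed counts is correct.
- **Failing to reach significance with one or two cases is a fault of the test.** It is low power, which the article concedes.

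**Conclusion.** The point holds as a minor improvement to a secondary outcome. A chi-square test is a defensible supportive analysis for H3 but a poor sole result if AP is rare. At an assumed common risk of 1% to 5% it is undefined in 74% to 21% of studies with 10 per group and in 55% to 5% with 20, and a single case gives only p = 0.36. If the cumulative AP risk is nearer 10%, an empty table is unlikely (4% and 0.2%) and the argument rests on what a p-value leaves unsaid. The conclusion assumes three equal groups of 10 to 20 and an AP risk that the article does not state.

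A reader might also infer that the analysis would produce a false claim of safety. The article does not say that a null result will be read that way. The risk is one of misreading, which intervals would reduce. H3 expects a difference while the Fig 1 legend expects no association; that is a separate matter, which intervals do not settle.

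**What to change.** In H3, state that the main AP result is the number and proportion of patients with AP in each of the three observed groups, with Clopper-Pearson 95% intervals, plus an exact 95% interval for the exposed-minus-unexposed difference among IPMN patients. Keep the chi-square test, or a pre-named mid-p exact version, as supportive. Add that only the intervals are reported if no AP occurs, and that a non-significant test is not read as evidence of safety.

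Any comparison with the general-population AP figure should be descriptive. It should be made only once a common observation window for AP has been set for all groups: the Analysis plan defines T0 for the two IPMN groups, in connection with progression, and gives none for GLP-1 RA patients without IPMN.

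The core change costs one or two sentences and no new data; the common window is a further decision, needed only for the population comparison. The downside is that the intervals will be wide (up to 31% for 0/10, up to 17% for 0/20) and will look less favourable than a non-significant p-value.

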### Ethics approval and consent to participate

The Ethic Committee “Commission cantonale d’éthique de la recherche sur l’être humain (CER-VD)” has approved this retrospective study (Application number 2025−00486) and given consent to participate. All patients have signed the general consent from one of the three participating institutions (S4 File). All modifications to the protocol will be communicated to the ethics committee as amendments. Data transfer agreement was signed by the three primary investigators at the three institutions prior to the beginning of the study. All data are handled with study ID and without identification number.

## Discussion

This study aims to provide preliminary insights into the potential impact of GLP-1 RAs therapy on the progression and clinical outcomes of IPMNs. A better understanding of the relationship between GLP-1 RA exposure and IPMNs may help address current safety uncertainties and support clinical decision-making in this complex patient population.

Several limitations must be acknowledged. The retrospective design introduces inherent risks of selection and information bias, while the relatively small sample size limits statistical power and the ability to detect modest associations. Patient identification may be incomplete, as GLP-1 RAs prescriptions may have been initiated by healthcare providers outside the participating institutions or inconsistently documented and therefore not fully captured in institutional records. Furthermore, initiation of the treatment may have been influenced by clinical judgement and recent literature implying a possible link between GLP1 Ras use and pancreatitis or pancreatic cancer, introducing potential prescription bias. In addition, the relatively recent and rapidly increasing widespread use of GLP-1 receptor agonists may limit the ability to assess long-term effects on IPMN evolution. As a result, potential late modifications or clinically relevant changes may not yet be detectable within the available follow-up period.

Therefore, the results should be interpreted as hypothesis-generating. Despite these limitations, this study addresses an important gap in the current literature and may serve as a basis for future prospective, multicentre studies.

## Abbreviations

IPMNs: Intraductal papillary mucinous neoplasms
GLP-1 RAs: Glucagon-like peptide-1 receptor agonists
AP: Acute pancreatitis
HFR: Fribourg Cantonal Hospital, Switzerland
HUG: Hopitaux universitaires Geneve, Switzerland
CER-VD: Commission cantonale d’éthique de la recherche sur l’être humain
